# Effects of an exclusive human-milk diet in preterm neonates on early vascular aging risk factors (NEOVASC): study protocol for a multicentric, prospective, randomized, controlled, open, and parallel group clinical trial

**DOI:** 10.1186/s13063-021-05445-9

**Published:** 2021-07-31

**Keywords:** Neonatology, Prematurity, Preterm, Human milk, Human-milk-based fortifier, Cardiovascular risk

## Abstract

**Background:**

Preterm birth accounts for approximately 11% of all livebirths globally. Due to improvements in perinatal care, more than 95% of these infants now survive into adulthood. Research has indicated a robust association between prematurity and increased cardiovascular risk factors and cardiovascular mortality. While the innate adverse effects of prematurity on these outcomes have been demonstrated, therapeutic strategies on the mitigation of these concerning developments are lacking. The primary objective of the NEOVASC clinical trial is therefore to investigate whether the administration of a prolonged exclusive human-milk diet in preterm infants is capable of alleviating the harmful effects of preterm birth on the early development of cardiovascular risk factors.

**Methods:**

The NEOVASC study is a multicentric, prospective, randomized, controlled, open, and parallel group clinical trial conducted in four Austrian tertiary neonatal care facilities. The purpose of the present trial is to investigate the effects of a prolonged exclusive human-milk-diet devoid of bovine-milk-based food components on cardiovascular and metabolic risk factors at 1, 2, and 5 years of corrected age. Primary outcomes include assessments of fasting blood glucose levels, blood pressure levels, and the distensibility of the descending aorta using validated echocardiographic protocols at 5 years of corrected age. The test group, which consists of 200 preterm infants, will therefore be compared to a control group of 100 term-born infants and a historical control group recruited previously.

**Discussion:**

Given the emerging implications of an increased cardiovascular risk profile in the potentially growing population of preterm infants, further research on the mitigation of long-term morbidities in formerly preterm infants is urgently warranted. Further optimizing preterm infants’ nutrition by removing bovine-milk-based food components may therefore be an interesting approach worth pursuing.

**Trial registration:**

ClinicalTrials.govNCT04413994. Registered on 4 June 2020.

**Supplementary Information:**

The online version contains supplementary material available at 10.1186/s13063-021-05445-9.

## Introduction

### Background

According to the World Health Organization (WHO), noncommunicable diseases (NCDs) are the world’s leading cause of death. Among NCDs, cardiovascular diseases (CVDs) are the most common ones, responsible for an estimated 17.8 million (31.8 %) deaths in 2017, and are therefore the single leading cause of global mortality [1, 2]. While family history and unhealthy lifestyle factors are undoubtedly associated with the development of CVDs, further research has identified early-life exposures as additional risk factors. Based on Barker’s “fetal origins of adult disease” hypothesis, adverse conditions in the intrauterine and perinatal environment may permanently alter physiologic circuits and organ function. Initially intended to aid survival, these adaptions may prove disadvantageous in the long-term by putting individuals at risk for the development of chronic cardiovascular and metabolic disorders [3, 4]. Recent evidence has suggested that preterm birth plays an important role in the fetal/neonatal programming of future morbidity [5] and mortality [6–9]. According to the most recent WHO estimates, preterm birth (< 37 weeks’ gestation) accounted for 10.6% of all livebirths worldwide with tendencies potentially increasing over time in middle- and high-income countries [10]. Due to advances in perinatal care [11, 12], the vast majority of these preterm infants now survive into adulthood [6–8]. However, several studies have shown an association between preterm birth and cardiovascular risk factors such as elevated blood pressure (BP) levels [13–16], hypertension [13, 17, 18], and type 1 or type 2 diabetes mellitus [19, 20], respectively. Compared with children born at term (≥ 37 weeks’ gestation), formerly preterm infants further display significantly reduced distensibility and increased stiffness of the descending abdominal aorta at preschool age [21], indicating initial signs of early vascular aging [22]. Mother’s milk is the optimal source of nutrition for all infants [23]. As for many preterm infants, the nutritional value of human milk is commonly enhanced by the use of fortifiers to meet their special needs. In cases with insufficient amounts of mother’s own or donor human milk, preterm formula is routinely used. Research has suggested potential benefits of an exclusive human-milk-based diet (i.e., the combination of mother’s own or donor human milk with human-milk-based fortifiers) on outcomes such as rates of necrotizing enterocolitis (NEC), duration of parenteral nutrition, and risk of late-onset sepsis and mortality when compared to a diet containing any bovine-milk-based products [24–27]. While the favorable effects of human milk on the development of the abovementioned cardiovascular and metabolic outcomes have been demonstrated despite methodological limitations [28, 29], no study has yet investigated the possible benefits of an exclusive human-milk-diet devoid of bovine-milk-based dietary components in preterm infants during the vulnerable preterm period on these very outcomes.

### The NEOVASC study

The NEOVASC study is a multicentric, prospective, randomized, controlled, open, and parallel group clinical trial conducted in four Austrian tertiary neonatal care facilities (Medical University of Innsbruck, Paracelsus Medical University Salzburg, Medical University of Vienna, Academic Teaching Hospital Feldkirch). The purpose of the present trial is to investigate the superiority of a prolonged (until 36 weeks’ gestation) exclusive human-milk-diet devoid of bovine-milk-based food components on cardiovascular and metabolic risk factors. By following formerly preterm infants until the corrected age of 5 years, we intend to facilitate research findings on the impact of specifically targeted early dietary interventions on long-term cardiovascular health. Previous research has shown that increases in BP [30, 31], alterations in glucose homeostasis [30, 32, 33], and vascular integrity [21] are visible even in early childhood following preterm birth. Given the inverse correlation between gestational age and adulthood diabetes [20] and hypertension [13, 18], respectively, we anticipate markedly significant results should our intervention in these preterm infants prove effective.

## Methods/design

### Study population and eligibility

#### Preterm-born infants

Extremely preterm infants with a birth weight between 500 g and 1250 g will be eligible to undergo randomization in the NEOVASC study. This particular weight range was chosen in accordance with previous clinical trials on exclusive human-milk diet [24–27]. Furthermore, written informed consent from the mother will be obtained in order to enroll participants. Exclusion criteria are birth weight < 500 g or > 1250 g, inborn errors of metabolism (e.g., galactosemia, phenylketonuria), not having been NPO or fed exclusive human-milk diet prior to enrollment, presence of major congenital malformation, presence of intestinal perforation or stage II NEC prior to enrollment, parents unwilling to sign informed consent, and lastly the inability to participate for any reason based on the study investigator’s judgment (e.g., unlikely to survive the study period).

#### Term-born infants

For the control group, term-born (≥ 37 weeks’ gestation) children with an adequate birth weight will be recruited at 5 years of age. Written informed consent will be obtained from the parent(s) or legal guardian(s) prior to enrollment. Exclusion criteria are acute and chronic illness or the unwillingness of the parent(s) to sign the informed consent form.

### Randomization, study groups, and interventions

Randomization of preterm infants will be done electronically by the use of permuted blocks (block size = 4) within a stratified randomization. The allocation sequence will be generated by the study’s statistician and provided to the principal investigators in the form of a conventional unblinded randomization table. Stratification variables are the study site and birth weight (< 1000 g and 1000–1250 g). On the basis of ethical considerations, twins are always randomized into the same study group. Preterm neonates will be randomized to either (i) an exclusive human-milk-based diet composed of mother’s milk or pasteurized donor human milk in combination with a human-milk-based fortifier (Humavant^TM^ +4,+6; Prolacta Bioscience, Inc.) until 36 weeks of gestation (Randomized Study Product Group) or (ii) mother’s milk or pasteurized donor human-milk (as long as available) in combination with a human-milk-based fortifier (as long as human milk is available) until 32 weeks’ gestation and thereafter mother’s milk or pasteurized donor human milk with a bovine-milk-based fortifier or preterm formula (Randomized Control Group) in a 1:1 ratio. Feeding will be done by protocol in which fortification will begin when the infant is receiving 80–100 ml/kg/day of enteral nutrition. After 36 weeks’ gestation, human milk with a bovine-milk-based fortifier or preterm formula will be used in both groups. While blinding of study groups is always desirable in randomized studies, this is not possible for this study due to the nature of the intervention. As a control group, term-born age-matched infants will be included (Term-born Control Group). Infants within this control group will be recruited in kindergartens at 5 years of age. The results of the present study will further be compared to a group of very preterm infants enrolled for prior clinical studies at the Medical University of Innsbruck (Historical Control Group) [21, 30, 34]. See Figure S1 for a graphic display of the study design. The description of the overall study design is in agreement with the 2013 SPIRIT checklist (see Fig. 1).

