### Informed consent procedure and withdrawal

Expecting parents of potential participants will be invited by the respective principal investigators and/or explicitly permitted colleagues to enroll their preterm infants before or in a timely manner after delivery. Since additional data on the course of pregnancy will be gathered as well, written informed consent about the participation of preterm infants must be explicitly obtained from the infant’s mother. As for study participants in the term-born control group, written informed consent can be obtained from either parent or legal guardian. Subjects and their legal guardians have the right to withdraw consent fully or partially at any time and for any reason. All data until the point of withdrawal will be included in the final analysis. However, no further information will be collected. Protocol changes will be communicated to interested parties using the clinicaltrials.gov platform. Whenever protocol changes will affect study participants, informed consent will be obtained using an updated informed consent form.

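### The allocation table is given openly to the principal investigators, who also take part in enrolment, so allocation is not concealed as written and selection bias is possible

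*Protocol article*

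**What the plan says.** Three sections of the protocol article bear on this.

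- **Randomization, study groups, and interventions.** The method is given as follows: "Randomization of preterm infants will be done electronically by the use of permuted blocks (block size = 4) within a stratified randomization". The strata are study site and two birth-weight classes, the ratio is 1:1, and twins always share an arm. On custody of the list: "The allocation sequence will be generated by the study’s statistician", and it is then "provided to the principal investigators in the form of a conventional unblinded randomization table". The section adds that the groups cannot be blinded because of the nature of the intervention.
- **Informed consent procedure and withdrawal.** Parents are "invited by the respective principal investigators and/or explicitly permitted colleagues to enroll their preterm infants", either before delivery or soon after it.
- **Study population and eligibility, Preterm-born infants.** The last exclusion criterion is "the inability to participate for any reason based on the study investigator’s judgment", with poor prospects of survival as the example.

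The article describes no step that keeps an assignment hidden until an infant is enrolled.

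**The concern.** Blinding and concealment are different safeguards. Blinding concerns who knows the arm after assignment, and here it is reasonably ruled out. Concealment concerns who knows the arm before the decision to enrol, and any open trial can have it. The article gives the sequence, openly, to people who approach parents. It also leaves an exclusion to the investigator's judgment.

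The randomized comparison carries the superiority claim. If knowledge of the next arm influenced which infants were approached, when they were randomized, or which were judged unable to take part, the arms could differ at entry in prognosis. The independent variables named for the regression analyses (sex, gestational age, birth weight, ponderal index) do not record a clinician's impression of an infant. Adjustment for them could not be relied on to remove such a difference.

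**Working it through.** **1. What a table holder knows.** There are 4 sites ("conducted in four Austrian tertiary neonatal care facilities") and 2 birth-weight classes, so 4 × 2 = 8 strata, with two lists at each site. With 200 infants this averages 200 / 8 = 25 per stratum. A holder can read the next entry in each stratum. Once birth weight is known, the stratum is known, and so is the infant's arm. A principal investigator who receives only the site's own part still sees every upcoming local assignment, because site is a stratification variable.

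**2. What could be worked out without the table.** This uses "permuted blocks (block size = 4) within a stratified randomization" and assumes that each infant takes one slot, that past assignments are known at the site, and that the block size is known. There are 6 equally likely orders of AABB.

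- Certain assignments: the fourth always, and the third when the first two are alike (probability 1/3). That is 1 + 1/3 = 1.333 of 4, or 33.3%.
- Best guess (always the arm that is behind): 0.5 + 2/3 + 2/3 + 1 = 2.833 of 4, or 70.8%. Under full concealment it is 50%.
- Known fixed block of 6: 25.0% certain, 68.3% guessed correctly. Known fixed block of 8: 20.0% and 66.6%.
- Sizes 2, 4 and 6 equally likely: expected correct guesses are 1.5, 2.833 and 4.1 (the last is 6 × 0.6833), so (1.5 + 2.833 + 4.1) / 12 = 70.3%. The guess needs no knowledge of block size. Varying the size lowers the share of certain assignments but hardly changes the guess rate.

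Custody of the table is therefore the main issue, and block size is secondary.

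**3. The plan's own sample size.** For d = 0.4, two-sided alpha 0.05 (the article does not state sidedness) and power 0.8, the required number is 99 per arm by the normal approximation and 99.1, so 100, by the t-test. At 100 per arm the t-test power is 0.804. The stated group size reproduces and is not in question.

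**4. Illustration of what a shift would do.** The target difference in systolic pressure is 102 − 99 = 3 mmHg at d = 0.4, which implies an SD of 3 / 0.4 = 7.5 mmHg. The standard error of the difference is 7.5 × √(2/100) = 1.061 mmHg. If the diet has no effect but selection shifts the mean difference by s, the two-sided rejection rate is Φ(s/1.061 − 1.96) + Φ(−s/1.061 − 1.96).

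| Assumed shift s (mmHg) | In SD units | s / 1.061 | Rejection rate |
|---|---|---|---|
| 0.5 | 0.067 | 0.471 | about 8% |
| 1 | 0.133 | 0.943 | about 16% |
| 2 | 0.267 | 1.886 | about 47% |

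The shifts are assumptions, and nothing in the documents supports any one of them. The calculation treats one unadjusted test, whereas the plan applies Benjamini-Hochberg across outcomes.

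**The case against.** The strongest reply is that the article condenses a longer protocol. Randomization is said to be electronic, and protocol version 4.7, which is not shown, may explain how the table and the electronic step fit together. That is possible, but the article does not merely leave concealment out: it states who receives the sequence and in what form. An electronic step hides nothing from someone who holds the open table. At the least, the two statements need reconciling.

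A reader might infer more than the text supports:

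- **That every enroller sees the whole table.** The article does not say the table is complete, when it is handed over, or that permitted colleagues and every investigator who may exclude an infant have access to it.
- **That every allocation is known in advance.** Parents may be approached before delivery, when the birth-weight class may still be uncertain. A holder then knows the next entry in each class but not always which one will apply.
- **That a third of assignments are certain from the block size alone.** This holds only if each infant takes one slot. Twins share an arm, and the article does not say whether a pair uses one slot or two.
- **That bias has occurred, or is of a known size.** Nothing in the documents shows this.

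Some features may limit any bias. Stratification restrains steering by birth weight between the classes, though not within them. Both arms are planned to receive human milk with a human-milk-based fortifier until 32 weeks, subject to availability in the control arm, which plausibly weakens the motive to steer at entry. A covariate-adjusted model is also planned. None of these restores concealment. A block of 4 is itself defensible with about 25 infants per stratum.

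**Conclusion.** The point stands in this form: as written, allocation is not concealed from a principal investigator who holds the table, and the same document gives principal investigators a part in enrolment and gives the investigator discretion over exclusion. Selection bias is therefore possible in the comparison on which the trial's claim rests. This must be fixed.

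The conclusion rests on the plain meaning of the custody sentence, not on any calculation. It assumes that the table reaches the principal investigators before enrolment in the relevant stratum is complete, which is the natural reading. The size of any bias is unknown. The false-positive rates above show only that a shift well below the 3 mmHg target would matter.

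**What to change.** **Essential.** Replace the custody sentence so that:

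- the sequence stays with the statistician or in a central electronic module, and no enrolling investigator holds it;
- each arm is released only after eligibility and consent have been recorded for that infant or twin pair;
- every screened infant is logged, with the reason for any discretionary exclusion;
- the trial report states which infants were allocated while the table was held at sites. Recruitment began on 7 October 2020, and concealment cannot be restored for those infants.

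If a concealed system is already in use, correcting the sentence is enough.

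**Optional and secondary.** Do not disclose block sizes to sites, and vary them for the remaining enrolment. This lowers the share of certain assignments but leaves the best-guess rate at about 70% against 71%. A new list may also cut a block short in each of the 8 strata, with an imbalance of up to 2 per stratum, or 8 × 2 = 16 if all fell the same way.

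**Cost.** System configuration and a short amendment. The trial already randomizes electronically and uses electronic data capture. The sample size does not change.

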### Sample size and statistical analyses

A group size of 100 preterm infants per study arm is sufficient to detect a lowering in systolic blood pressure from 102 mmHg (Randomized Control Group) to 99 mmHg (Randomized Study Product Group), a reduction of fasting glucose levels from 84 to 78.5 mg/dl, and an increase in the distensibility of the descending aorta from 76 to 85 kPa^−1^ × 10^−3^, respectively. Based on previous experience, the principal investigators are confident to recruit the intended number of study participants within a recruitment period of 36 months. Each of these calculations was performed considering a power of 0.8 by the use of two-sample *T*-test for independent samples with homoscedastic variances. The effect size for this clinical trial was based on Cohen’s *D* assuming an effect size of 0.4. All statistical analyses will be performed on an intention-to-treat paradigm with a significance level of 0.05. Multiple outcomes will be handled using the Benjamini-Hochberg procedure for controlling the false discovery rate. Distensibility and stiffness index β of the descending abdominal aorta and lipid profiles will be compared between groups with two-sample *T*-tests or the Wilcoxon rank-sum test as a primary analysis at any given time point (looking at change from baseline). However, an adjusted analysis using a general linear model will incorporate the potential time trends in the results, as well as relevant covariates. Relationships between elasticity and stiffness, or lipid profiles and independent variables (sex, gestational age at birth, birth weight, ponderal index) will be studied by univariate and multivariate regression analysis. Missing data will be imputed using a multiple imputation with chained equations approach. In the event of repeated missing data over time, the simplistic last value carried forward approach may be used. However, in order to evaluate the data from a sensitivity analysis perspective, a secondary analysis on a per-protocol basis will be performed. This analysis will only consider participants who were correctly randomized and have complete data sets.

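### Randomization is stratified by site and birth-weight class, but the test named as primary leaves both factors out; a model with the strata that also handles twin pairs would be a cheap improvement

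*Protocol article*

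**What the plan says.** All references are to the protocol article.

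- **Design.** The section on randomization, study groups and interventions specifies "permuted blocks (block size = 4) within a stratified randomization" and then "Stratification variables are the study site and birth weight", the latter in two classes (< 1000 g, 1000–1250 g). Allocation is 1:1. The section on the NEOVASC study names four centres, so there are 4 × 2 = 8 strata. The randomization section also states that "twins are always randomized into the same study group".
- **Primary test.** The section on sample size and statistical analyses compares distensibility, stiffness index and lipids by two-sample t-test "or the Wilcoxon rank-sum test as a primary analysis". Blood pressure and fasting glucose are not named in that sentence. For them the t-test appears only in the sample-size text, which sizes all three primary outcomes on it.
- **Adjusted analysis.** The next sentence adds that "an adjusted analysis using a general linear model will incorporate the potential time trends in the results, as well as relevant covariates". The covariates are not listed there. The separate regressions for elasticity, stiffness and lipids list sex, gestational age, birth weight and ponderal index, but not site.

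**The concern.** Stratified blocks keep the arms nearly balanced within each stratum, so differences between strata contribute almost nothing to the treatment contrast. The two-sample test does not use this: its standard error still contains the between-stratum variance. Where the strata are prognostic and infants are independent, the test is conservative and gives away some power.

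The strata could plausibly be prognostic. The article cites inverse relations of gestational age with hypertension and diabetes, to which birth weight is closely tied, and it lists birth weight as an independent variable for elasticity. Echocardiographic distensibility measured at four centres may also differ by operator and device. The sample size has almost no margin, and the article states no allowance for loss over five years, so even a few points of power are worth having.

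**Working it through.** **Inputs from the article:** 100 per arm, Cohen's d = 0.4, power 0.80, significance level 0.05, 8 strata, twins allocated together.

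**Assumptions (no figure in the article):** R², the share of outcome variance explained by the strata; 80 per arm as an illustration of attrition; the share q of infants in twin pairs; the within-pair correlation r.

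**1. The article's own figure.** With a two-sided test, n = 2(1.960 + 0.842)² / 0.4² = 98.1, so 99 per arm. The exact t solution is 99.08, so 100. Power at 100 is 0.807 (normal) or 0.804 (exact t). The stated size reproduces. A one-sided test would need 78, so two-sided 0.05 is implied.

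**2. Effect of leaving the strata out, infants independent.** The total SD is set to 1, so the nominal SE is √(2/n): 0.1414 at n = 100 and 0.1581 at n = 80.

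- SE overstatement = 1/√(1 − R²)
- True type I error of the unadjusted test = 2[1 − Φ(1.96/√(1 − R²))]
- Unadjusted power = Φ[(0.4/SE − 1.96)/√(1 − R²)]
- Adjusted power = Φ[0.4/(SE·√(1 − R²)) − 1.96]

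| R² | SE too wide by | Type I error, unadjusted | Power n=100, unadj. / adj. | Power n=80, unadj. / adj. |
|---|---|---|---|---|
| 0 | 0 | 0.050 | 0.807 / 0.807 | 0.716 / 0.716 |
| 0.05 | 2.6% | 0.044 | 0.814 / 0.827 | 0.721 / 0.738 |
| 0.10 | 5.4% | 0.039 | 0.820 / 0.847 | 0.726 / 0.760 |
| 0.20 | 11.8% | 0.028 | 0.834 / 0.885 | 0.738 / 0.807 |

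For R² of 0.05–0.20 the gain from adjusting is 1.3–5.1 points at 100 per arm and about 2–7 points at 80 per arm. Both tests are compared at the same R².

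**3. Simulation check.** Eight strata, blocks of 4, 200 independent infants, 3000 runs per setting. At R² = 0.20, type I error was 0.032 unadjusted and 0.048 adjusted; power was 0.819 and 0.875. At R² = 0 the two tests performed alike (power 0.807 and 0.806).

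**4. Twins act in the opposite direction.** When pairs share an arm, the variance of the contrast rises by about 1 + q·r. Combining this approximately with step 2, true variance / nominal variance = (1 − R²)(1 + q·r), and type I error = 2[1 − Φ(1.96/√ratio)].

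| Assumed twins | Twins alone | R² = 0.05 | R² = 0.10 | R² = 0.20 |
|---|---|---|---|---|
| q = 0.2, r = 0.5 (factor 1.10) | 0.062 | 0.055 | 0.049 | 0.037 |
| q = 0.4, r = 0.7 (factor 1.28) | 0.083 | 0.076 | 0.068 | 0.053 |

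The net error rate falls on either side of 0.05, depending on inputs that the article does not supply.

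**The case against.** The strongest reply is that nothing planned is lost. The trial is sized on an unadjusted t-test, that calculation reproduces, and for independent infants the unadjusted test keeps at least 0.80 power at 100 per arm for every R² tried. Birth weight is restricted to 500–1250 g and validated echocardiographic protocols are specified, so large stratum effects cannot be presumed. An adjusted model is also already planned. All of this stands. It limits the point to efficiency and calibration, but it does not remove the mismatch: the article gives primary status to the unadjusted comparison and treats the model as additional.

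Two stronger readings are tempting.

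- A reader might infer that the error bars are too wide and the test conservative overall. That follows only if infants are independent. The article places twins in the same arm, and the same unadjusted test ignores that.
- A reader might also count the open choice between t-test and Wilcoxon, or the unnamed covariates, as defects. A condensed article may leave such detail to the full protocol or the SAP, neither of which is shown.

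**Conclusion.** The point holds as a modest improvement. The factors that govern the randomization are missing from the analysis named as primary for distensibility (and for stiffness and lipids), and from the t-test used to size the trial for blood pressure and glucose.

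The size rests on an assumed R² of 5–20% and independent infants: an unadjusted SE 2.6–11.8% too wide, with power of 0.81–0.83 instead of 0.83–0.88 at 100 per arm, or 0.72–0.74 instead of 0.74–0.81 at an illustrative 80 per arm. If the strata are not prognostic, the cost is nil. The article does not support a claim that the trial is underpowered for this reason. Nor does it support a claim that the intervals err in a known direction: once twin pairs are allowed for, net type I error under the assumptions shown runs from about 0.037 to 0.076.

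**What to change.** For each of the three 5-year primary outcomes (blood pressure, fasting glucose, aortic distensibility), name one primary analysis: a linear model with arm, site and birth-weight stratum (< 1000 g, 1000–1250 g). Account for twin pairs through cluster-robust standard errors or a random effect for the pair. Report the adjusted mean difference with its 95% confidence interval, and keep the unadjusted t-test or Wilcoxon test as a sensitivity analysis. Further covariates such as sex and gestational age are optional.

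The two parts belong together. Adding the strata alone would remove the conservative offset and leave the twin correlation unmodelled.

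The cost is small: a change of wording before the 5-year data are analysed, plus a pair identifier in the analysis file. Site, birth-weight class and twin status are already needed to randomize, so no new data and no larger sample are required.

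### Twins are always allocated together, but the sample size and the named primary test for aortic distensibility treat every infant as independent, so standard errors are likely too small and the stated power has no allowance for pairs

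*Protocol article*

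**What the plan says.** Allocation (Randomization, study groups, and interventions): preterm infants are randomized 1:1 in permuted blocks of four. "Stratification variables are the study site and birth weight", the latter cut at 1000 g. On ethical grounds, "twins are always randomized into the same study group". The eligibility criteria do not exclude multiples, so both members of a pair can enter.

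Sizing (Sample size and statistical analyses): "A group size of 100 preterm infants per study arm is sufficient" for stated differences in systolic blood pressure (102 to 99 mmHg), fasting glucose (84 to 78.5 mg/dl) and distensibility (76 to 85). "Each of these calculations was performed considering a power of 0.8", with a two-sample t-test "for independent samples with homoscedastic variances" and "assuming an effect size of 0.4".

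Analysis (same section): the framework is an "intention-to-treat paradigm with a significance level of 0.05". Distensibility, the stiffness index and lipid profiles are compared by two-sample t-test or Wilcoxon rank-sum test as the primary analysis. An adjusted general linear model adds time trends and covariates. Benjamini-Hochberg handles multiple outcomes. No family term, random effect, clustered standard error or design effect is mentioned.

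**The concern.** When two siblings always share an arm, their correlation adds to the variance of that arm's mean, and so to the variance of the difference between arms. Twins share a pregnancy, a home and many genes, so a positive correlation in blood pressure, glucose and vessel elasticity at five years is the natural expectation. The t-test and the Wilcoxon test both take each infant as a separate piece of information and miss this extra variance. The adjusted model, as described, misses it too. Benjamini-Hochberg accepts the p-values it is given and cannot repair them.

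Two things are at stake: the validity of p-values and intervals from an unclustered test, and the truth of the 0.8 power claim once pairs are handled properly. They are alternatives, not two losses to be added together.

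**Working it through.** **1. The plan's own figure.** Inputs: d = 0.4, power 0.8, significance level 0.05, independent samples. The article does not state sidedness. The two-sided noncentral t gives n = 99.08, hence 100 per arm, and power at 100 per arm is 0.804. One-sided 0.05 would need 78 per arm and does not match. The stated size is therefore the two-sided result for fully independent infants, with no allowance for pairs. The implied standard deviations are 3/0.4 = 7.5 mmHg, 5.5/0.4 = 13.75 mg/dl and 9/0.4 = 22.5 distensibility units.

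**2. Effect of joint allocation.** Let f be the share of infants who belong to an enrolled pair and ρ the within-pair correlation. An arm of n infants holds fn/2 pairs, and each pair adds 2ρσ² to the variance of the sum. So Var(mean) = (σ²/n)(1 + fρ), and the design effect is DE = 1 + fρ.

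- True level of a nominal 5% unclustered test: 2[1 − Φ(1.96/√DE)].
- Power of a valid clustered test: noncentral t at d = 0.4 with 100/DE per arm.

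Both f and ρ are assumptions; the article gives neither.

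| f | ρ | DE | True level, unclustered test | Effective n per arm | Power, valid test |
|---|---|---|---|---|---|
| 0.10 | 0.3 | 1.03 | 5.3% | 97 | 0.79 |
| 0.20 | 0.3 | 1.06 | 5.7% | 94 | 0.78 |
| 0.20 | 0.5 | 1.10 | 6.2% | 91 | 0.77 |
| 0.30 | 0.5 | 1.15 | 6.8% | 87 | 0.75 |
| 0.40 | 0.7 | 1.28 | 8.3% | 78 | 0.70 |

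Simulated t-tests with 100 per arm (40,000 runs, no strata) gave 5.0% with no twins, 6.3% at f = 0.2, ρ = 0.5, and 6.8% at f = 0.3, ρ = 0.5.

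**3. Effect of the strata.** Allocation is stratified, but the named test is not adjusted for strata. If the strata explain a share R² of the outcome variance and are perfectly balanced, and ρ is the correlation within strata, the true variance relative to the one the test uses is about (1 − R²)(1 + fρ). The level exceeds 5% only when this is above 1, that is, when R² < 1 − 1/DE. The break-even R² is 1 − 1/1.03 = 0.03, 1 − 1/1.06 = 0.06, 1 − 1/1.15 = 0.13 and 1 − 1/1.28 = 0.22 for the matching rows above.

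Balance is imperfect in practice, so this was also simulated: 200 infants, eight strata (four sites by two weight bands), blocks of four, pairs allocated together, 6,000 null trials per setting, simulation error about 0.3 points. With R² of 5–10%, the unclustered t-test ran between 4.4% and 8.6%, depending on f and ρ. A linear model with stratum terms and standard errors clustered on mother ran between 4.6% and 5.9% over all settings.

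**4. Detectable difference at 100 per arm.** At power 0.8 the detectable difference grows by about √DE, that is, by 1.015 at DE 1.03 and 1.131 at DE 1.28:

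- systolic pressure: 3 × 1.015 = 3.0 to 3 × 1.131 = 3.4 mmHg
- glucose: 5.5 × 1.015 = 5.6 to 5.5 × 1.131 = 6.2 mg/dl
- distensibility: 9 × 1.015 = 9.1 to 9 × 1.131 = 10.2 units

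**The case against.** The strongest reply is that the harm is modest and its size unknown. Only pairs in which both infants qualify and both are analysed at five years count towards f. At a 10% share and ρ = 0.3 the excess is 0.3 percentage points. Stratified allocation with an unadjusted test works in the opposite direction and can bring the level back to 5% or below. All of this stands: a reader might infer that the false-positive rate certainly exceeds 5%, and the documents do not support that.

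Other stronger readings also go too far:

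- **All three primary p-values are affected.** The sentence naming the primary test covers distensibility, stiffness and lipids. For blood pressure and glucose the t-test appears only in the sizing, so an unclustered final analysis of those two is an extrapolation.
- **The planned test also loses the quoted power.** The 0.79–0.70 belongs to a valid clustered test. The unclustered test keeps roughly 0.80–0.78 (normal approximation), but at a level that is not controlled.
- **Twins straddling 1000 g break the stratification.** The article does not say that each twin takes its own slot. Which infant's weight sets the stratum is operational detail that an article may leave to the full protocol.
- **The sizing wording asserts that siblings are independent.** It is the usual name of the unpaired test. The evidence is that 100 per arm reproduces only without an allowance for pairs.

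A final reply is that an analysis plan may deal with twins. That does not answer the point, because the article itself fixes an unclustered primary test beside an allocation rule that creates clusters. A clustered primary analysis would depart from what is written.

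**Conclusion.** The allocation rule and the stated statistics do not fit together. Joint allocation of twins is legitimate and does not in itself bias the estimated difference. But the sample size and the named primary test for distensibility leave out the correlation that it brings in.

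With assumed twin shares of 10–40% and within-pair correlations of 0.3–0.7, the design effect is 1.03–1.28. Standard errors are then too small by a factor of 1/√1.03 = 0.99 to 1/√1.28 = 0.88, and nominal 5% tests run at about 5.3–8.3%. Prognostic strata would reduce this, possibly to 5% or below. An excess is likely but not certain.

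The power statement is the firmer part. The 0.8 rests on full independence with almost no slack (0.804), and under the same assumptions a valid clustered test has about 0.79–0.70 before any loss to follow-up.

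**What to change.** Keep the joint allocation and make two changes.

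1. **Analysis.** For distensibility, blood pressure and fasting glucose, name as the primary analysis a linear model with treatment arm and the stratification factors (site and birth-weight band), with standard errors clustered on mother or a random intercept for mother. Use the same model in the imputation-based and per-protocol analyses. Including the strata also removes the offsetting conservatism, so that the stated level is close to the true one.
2. **Sample size statement.** State an assumed twin share and within-pair correlation, with their source, and restate the power, or the detectable difference, at 100 per arm. Clustering the analysis alone would leave the 0.8 uncorrected.

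The cost is a few sentences and a record of which infants share a mother. The price is slightly wider intervals and a slightly lower stated power. Raising the number of infants is not required if the lower power or larger detectable difference is accepted openly. The first patient entered on 7 October 2020 and the primary outcomes are measured at five years, so none can exist before October 2025 (2020 + 5). The change can therefore be fixed before any primary outcome is seen.
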